## Abstract

In times where only a few novel antibiotics are to be expected, antimicrobial resistance remains an expanding global health threat. In case of chronic infections caused by therapy-resistant pathogens, physicians have limited therapeutic options, which are often associated with detrimental consequences for the patient. This has resulted in a renewed interest in alternative strategies, such as bacteriophage (phage) therapy. However, there are still important hurdles that currently impede the more widespread implementation of phage therapy in clinical practice. First, the limited number of good-quality case series and clinical trials have failed to show the optimal application protocol in terms of route of administration, frequency of administration, treatment duration and phage titer. Second, there is limited information on the systemic effects of phage therapy. Finally, in the past, phage therapy has been applied intuitively in terms of the selection of phages and their combination as parts of phage cocktails. This has led to an enormous heterogeneity in previously published studies, resulting in a lack of reliable safety and efficacy data for phage therapy. We hereby present a study protocol that addresses these scientific hurdles using a multidisciplinary approach, bringing together the experience of clinical, pharmaceutical and molecular microbiology experts.

## 1. Introduction

Each year, over 700,000 people die due to drug-resistant infections. Without policies to stop the growing spread of antimicrobial resistance, this alarming number has been predicted to increase up to 10 million deaths every year by 2050 [1]. Pathogens such as methicillin-resistant *Staphylococcus aureus* (MRSA) and multidrug-resistant *Pseudomonas aeruginosa* (MDR-PA) present a significant health threat [2]. Within the healthcare setting alone, for example, MRSA infections are currently estimated to affect over 150,000 patients annually in the European Union, resulting in additional in-hospital costs of 380 million euros for EU healthcare systems [3]. Therefore, the World Health Organization (WHO) advocates increasing research focused on antimicrobial resistance [4]. Nevertheless, there is relatively limited interest from pharmaceutical companies to engage in the process of antibiotic drug development, particularly considering the potential restrictions on the use of any new antibiotics and the risk of rapid resistance development [4]. In addition, some pathogens are able to form biofilms, which makes them inaccessible to the human immune system and intrinsically resistant to antibiotics [3]. Furthermore, the close proximity of bacteria in a biofilm environment facilitates the dissemination of antibiotic-resistance genes through horizontal gene transfer, thereby increasing its recalcitrance to antibiotic treatment [5,6]. Therefore, especially for (chronic) infections caused by (multidrug-) resistant strains, treatment options are limited. This often compels physicians to take therapeutic measures with an important impact on the patient, such as lifelong suppressive antibiotics or amputation of the affected limb. For the abovementioned reasons, scientists are urgently seeking alternatives for antibiotics. One of these strategies is bacteriophage (phage) therapy.

Despite the promising clinical outcomes described in previous reports, these clinical applications have revealed some important hurdles that need to be overcome. First, the limited number of well-documented case series and clinical trials have failed to show the optimal application protocol in terms of route of administration, frequency of administration, treatment duration and phage titer. Second, there is limited information on the systemic effects of phage therapy. Finally, in the past, phage therapy has been applied intuitively in terms of phage selection and their combination in phage cocktails. These critical knowledge gaps regarding the safety and efficacy of phage therapy have contributed to the fact that competent authorities are hesitant towards the more widespread implementation of phage therapy in Western clinical practice. In Belgium, the application of phage therapy has a regulatory framework as magistral preparations [7]. In this regard, our center has approved the application of phage therapy as standard-of-care only in patients for whom no curative treatment alternatives (antibiotic and/or surgical) are available (‘last-resort cases’). A multidisciplinary phage task force, referred to as the Coordination group for Bacteriophage therapy Leuven (CBL), was therefore set up. Using this multidisciplinary approach, the first treatment successes in our center were already reported [8]. The CBL screens patients with difficult-to-treat infections, evaluates who could benefit from phage therapy and sets up the treatment protocol. With this study, the CBL aims to gain insight in the safety and efficacy of phage therapy by integrating and optimizing phage therapy in three distinct medical disciplines (with three distinct routes of administration), facilitating long-term follow-up of patients. We acknowledge that in this target population, where the infection will already be at an advanced stage, timing will be of the essence. With this study and the safety data it will generate, we hope to be able to broaden the indications for phage therapy in the future.

## 2. Materials and Methods

### 2.1. Study Objectives

The main objective of the study is to collect the safety and efficacy data of patients diagnosed with a difficult-to-treat musculoskeletal infection (MSI), chronic rhinosinusitis (CRS) or sepsis who have been treated with phage therapy. Specifically, this study aims at:-Implementing phage therapy in three medical disciplines and creating a prospective patient registry;-Gaining insight in the kinetics of phage therapy using three different routes of administration;-Characterizing the interaction between phage and bacteria and optimizing future phage cocktails by applying a genome-based approach.

### 2.2. Study Design

This is a prospective, monocentric and observational registry. In consultation with the hospital’s Ethics Committee, phage therapy is considered to be standard-of-care only in patients with difficult-to-treat infections for whom curative treatment alternatives (antibiotic and/or surgical) are not available (‘last-resort cases’). Whether the patient will receive phage therapy (phage treatment group) or a standardized non-curative (e.g., amputation, chronic antibiotic suppression) treatment (control group) depends solely on the susceptibility of the causative pathogen(s) against the available phages. More specifically, in case active phages are not available against all causative pathogen(s), the patient will not undergo phage therapy.

### 2.3. Study Population

The selection of infectious indications for phage therapy in this study protocol is based on the clinical expertise of a multidisciplinary team. Moreover, these indications represent different levels of complexity, from intraoperative and local (MSI) to topical, intranasal (CRS) and systemic, intravenous (sepsis) applications.

#### 2.3.1. Sample Size Calculation

Since data on the application of phage therapy for MSI, CRS and sepsis are currently scarce, we are unable to perform a power analysis due to the absence of an objective effect size. The main aim of this registry is to obtain safety and efficacy data. Based on previously received requests for phage therapy, an estimated 150 patients will be included. Furthermore, within this patient population, approximately 75 will have a positive phagogram and can therefore be treated with phage therapy.

#### 2.3.2. Eligibility

When the treating physician presumes his or her patient may benefit from phage therapy, the patient is presented to the CBL. The CBL will look into the patient’s medical history and determine if past treatments were adequate and if there are any other curative (surgical or antibiotic) treatment options available. In most cases, the causative pathogen is known at the time of presentation to the CBL. They will therefore also evaluate if phages are available in the phage bank against the previously isolated bacterial species. If that is the case and if no alternative curative treatments are available, the patient is eligible for inclusion in the PHAGEFORCE study. The study flowchart including the aforementioned application procedure is presented in Figure 1.

#### 2.3.3. Inclusion Criteria

All patients:-Diagnosed with a difficult-to-treat MSI, CRS or sepsis, and;-For whom all previous treatments (surgical and antibiotic) have failed or for whom no other curative treatment options are available (i.e., ‘last resort cases’, based on the CBL assessment), for example in case of bacterial resistance, and;-For whom phages targeting the isolated bacterial species are available in the phage bank, and;-Who have given informed consent to have their data collected in a patient registry.

#### 2.3.4. Exclusion Criteria

All patients:-With an infectious disease other than MSI, CRS or sepsis, and/or;-For whom standard curative treatment alternatives are still available, and/or;-For whom phages targeting the isolated bacterial species are not available in the phage bank, and/or;-Who refuse to give their informed consent.

### 2.4. Study Procedures

After the CBL has deemed the patient eligible for phage therapy, informed consent will be asked from the patient, either at the outpatient clinic or at the hospital ward. The informed consent covers prospective data collection prior to, during and after (phage) treatment. Study-specific variables that will be collected for each indication are listed below.

#### 2.4.1. Baseline Parameters

When informed consent is obtained, parameters regarding the patient’s demographics, medical history and comorbidities, as well as details on the current infection are collected. Patient demographics comprise variables including the patient’s age, sex, weight, height and ethnicity. The medical history includes pre-existing conditions (e.g., cardiovascular diseases, asthma, diabetes). Any concomitant medications associated with these pre-existing conditions will be recorded. The American Society of Anesthesiologists (ASA) score for MSI patients and the baseline Lund–Kennedy (based on nasal endoscopy), Modified Davos (based on nasal endoscopy) and Lund–Mackay (based on CT evaluation) scores for CRS patients will be recorded. For sepsis patients, the baseline Sequential Organ Failure Assessment (SOFA) score will be collected. Radiographic images and/or clinical pictures are taken as part of the standard-of-care.

If no recent cultures are available for susceptibility testing, bacteriological samples will be taken and cultured. For MSI patients, this includes intraoperative deep tissue cultures taken during a surgical debridement. Nasal swabs and hemocultures will be taken from CRS and sepsis patients, respectively. The isolated pathogens will be sent to the Queen Astrid Military Hospital (QAMH) for susceptibility testing against phages in their phage bank. Depending on the susceptibility of the isolates, also referred to as the ‘phagogram’, the patient can be included in the phage treatment group or the control group where no alternative curative treatment options are available. In case of polymicrobial infections, all isolated bacterial species have to be susceptible to the available phages. Furthermore, the CBL will set up the treatment plan accordingly and document this in the patient’s medical file. Therefore, in this study, there are two types of standard-of-care, as displayed in Figure 2 and defined below.

#### 2.4.2. Treatment-Specific Parameters: Phage Treatment Group

If all eligibility criteria are met and a positive phagogram is obtained, the patient will be included in the phage treatment group. The CBL will design the treatment protocol and document it in the CBL final treatment plan, which is also registered in the patient’s medical file. Phages will be administered locally, through a draining system for MSI patients (as previously described [8]), intranasal for CRS patients and intravenously for sepsis patients. The phages that will be used are produced according to a monograph at the QAMH [7]. Furthermore, these phages are well-characterized, in that the genetic sequence and therefore the confirmation of each phage’s strictly lytic profile and absence of undesired genetic determinants (e.g., toxins and antibiotic-resistance genes) are available. These analyses are verified independently by Sciensano, the Belgian federal research institute for public health, and summarized in a so-called genetic passport. Moreover, each batch of phages (phage stock) produced at the QAMH is quality controlled by Sciensano before it can be used in humans [7,8]. Furthermore, phage stock titers will be determined frequently and prior to each dilution for phage therapy. For each individual phage that will be used, stability tests of the diluted preparations will also be performed for the different indications. In this way, we know how frequently we need to prepare new diluted preparations during the treatment to maintain a therapeutic target titer.

Improvements in pharmacological insights during phage therapy development is critical, particularly towards obtaining a better understanding of treatment failures [9]. As it is likely that the systemic exposure of a virulent phage is significantly modified due to its adsorption to the susceptible bacterial cells causing the infection, it becomes difficult to extrapolate the systemic exposure of other antimicrobial drugs to that of the phages. Furthermore, virulent phages multiply within their host and, as a result, while classic antibiotics decay over time, bacteriophage titers increase in the presence of a susceptible host [10]. Multiple samples will be taken (as detailed in Table S1) to monitor the patient and treatment progress. These samples will also be used to gain insight into the physiology of the phages during phage therapy, as detailed below.

##### Phage Dynamics

Assessment of Safety

One of the principal aims of this study is to evaluate the safety profile of the applied phage therapy protocols. Patients treated with phage therapy are closely monitored during phage therapy. Their clinical parameters (e.g., heart rate, blood pressure, oxygen level, temperature, respiratory rate) will be collected as detailed in Table S1 and stored in the patient registry. In addition, it is a standard-of-care to have several blood tests and samples analyzed, as listed in Table S1, to monitor the general health status of the patients. The following (blood) laboratory tests are required for monitoring (and optimization) of the phage therapy regimen and are therefore considered standard-of-care for patients treated with phage therapy:-Complete blood count (CBC);-Basic metabolic panel;-Inflammatory parameters;-Lactic acid, Creatine kinase;-Liver function tests;-Antiphage antibodies (serum);-Phage titration and isolation from draining fluid (MSI), nasal swabs (CRS) or serum (sepsis).

Even though no phage-related toxicity has been described or is to be expected, monitoring these parameters closely ensures that quick action can be undertaken in case of abnormalities. In this study, only adverse events or complications directly related to the condition or treatment of the infection will be collected. Specifically, for sepsis patients, only those safety parameters which could theoretically be related to the administration of phage therapy will be recorded in the patient’s digital medical record and in the patient registry. Reporting all untoward medical events on the intensive care unit (ICU) would not be practically feasible nor relevant, given the heterogeneity of the population and its inherent susceptibility to various medical events and complications. In case an adverse event (AE) or serious adverse event (SAE) occurs during the study period, this will be documented in the registry. The investigators and study personnel will seek information on AEs during each patient contact until three months after the final phage administration. All events that can be related to the infection or treatment of infection, whether reported by the patient or noted by the study personnel, will be recorded in the patient’s medical record and in the patient registry within a reasonable time after becoming aware. If available, the diagnosis will be reported on the AE page, rather than the individual signs or symptoms. If no diagnosis is available, the investigator will record each sign and symptom as individual AEs. Each AE will be followed up until resolved or until the end of the patient’s study participation, whichever occurs first. An independent data safety monitoring board (DSMB) is also set up for this study to help monitor the safety of phage therapy in our center. The DSMB consists of infectious disease physicians, intensive care specialists, pneumologists, clinical pharmacists, microbiologists and surgeons. For every 25 patients who are included, a report will be provided to the DSMB. They will go over any possible AEs, evaluate the overall outcome and provide feedback to the CBL.
Assessment of Efficacy

To assess the potential of phage therapy with respect to infection eradication, a combination of quantitative and qualitative outcome measures will be evaluated. As stated above, blood laboratory test results and clinical parameters will be collected to monitor the evaluation of the patient’s health status during treatment. The bacterial load during and after phage therapy will be measured. Several bacterial cultures will be taken from all patients. For CRS patients this entails nasal swabs, for sepsis patients this includes hemocultures. In case of MSI, it is not feasible to have multiple deep tissue cultures taken after the wound has been closed. As an alternative, during phage therapy, fluid collected in the draining system that is used for the application of phage therapy will be cultured. As these draining tubes are typically removed at the end of phage therapy, cultures can no longer be obtained during the follow-up period, unless there is a need for revision surgery (i.e., in case of recurrence of infection). Therefore, the main outcome measure for MSI patients is a disease-free period of at least one year after cessation of therapy. The bacteria and phages that are isolated from the various samples described above and listed in Table S1, will be stored for further analysis at −80 °C and 4 °C, respectively (see Section 2.5. Translational Research).

For CRS patients, specific clinical and quantitative outcome measures are available. These include endoscopic (Modified Davos, Lund–Kennedy), radiological (Lund–Mackay) and combined (European Position Paper on Rhinosinusitis and Nasal Polyps (EPOS) criteria for controlled or uncontrolled CRS) scoring systems, which will be collected and compared before, during and after phage therapy. Moreover, to evaluate the olfactory function in CRS patients, smell tests (Sniffin’ Stick test) will be carried out before and after phage therapy. For sepsis patients, the SOFA score will be recorded before, during and after treatment. The SOFA score is an internationally used score to objectively determine the degree of multiple organ failure in critically ill patients. A (rapid) decrease of the SOFA score (delta SOFA) is associated with a better survival and vice versa. Delta SOFA is defined as the difference between the SOFA score at baseline (prior to phage therapy) and the SOFA score at the final day of phage therapy.

Regarding qualitative outcome measures, patient-reported outcomes (PROs) will be collected from CRS and MSI patients. These include the PROMIS (patient-reported outcomes measurement information system) on global health and pain interference (for both CRS and MSI patients), PROMIS on physical function (for MSI patients) and the Sino-Nasal Outcome Test-22 (SNOT-22) and Visual Analogue Scale (VAS) for CRS patients.

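### The rules for recording adverse events conflict, the sepsis rule screens on phage-relatedness before recording, and collection in controls is undefined

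*Protocol article*

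**What the plan says.** Safety is central to the study. Section 2.1 states: "The main objective of the study is to collect the safety and efficacy data of patients diagnosed". The Assessment of Safety text in section 2.4.2 adds: "One of the principal aims of this study is to evaluate the safety profile of the applied phage therapy protocols".

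That same text then gives four statements on what is recorded:

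1. A general restriction: "only adverse events or complications directly related to the condition or treatment of the infection will be collected".
2. A narrower one for sepsis: "only those safety parameters which could theoretically be related to the administration of phage therapy will be recorded".
3. An unconditional statement: "In case an adverse event (AE) or serious adverse event (SAE) occurs during the study period, this will be documented in the registry".
4. A looser form of the general restriction: "All events that can be related to the infection or treatment of infection" are to be recorded.

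The reason given for the sepsis restriction is that "Reporting all untoward medical events on the intensive care unit (ICU) would not be practically feasible nor relevant". The paragraph opens with "Even though no phage-related toxicity has been described or is to be expected".

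Staff actively ask about AEs until three months after the last phage dose. All of this stands in the section headed for the phage treatment group. Section 2.4.4, on controls, covers blood and culture results, stored isolates, questionnaires, and follow-up for one year from the CBL's final treatment plan. It does not mention AEs. Section 2.6 plans summaries by treatment received, with complications reported per patient and per event.

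**The concern.** Relatedness is normally a judgement made about an event already on file. Here, under statements 1, 2 and 4, it decides whether the event is filed at all. That matters most in sepsis, where phages are given intravenously and where the Introduction names limited knowledge of systemic effects as a gap. A harm nobody anticipated is the kind least likely to look theoretically related to phage, and the staff judging it work from a text that expects no toxicity.

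Two things are at stake. First, two people following the same text could build different AE tables, so a low count could reflect the rule applied and not the treatment. Second, without a defined AE rule and window for controls, the AE summary by treatment received cannot show whether an event is background for last-resort patients. The Discussion faults earlier phage studies for inconsistent AE reporting and for not always describing how AEs were collected. The present text risks the same criticism.

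**Working it through.** The article states no AE rate, no sepsis count and no power calculation, so there is no figure to reproduce. The check is to apply each rule to the same hypothetical events.

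| Event | Directly related to infection or its treatment (1) | Sepsis: theoretically phage-related (2) | Any AE or SAE (3) | Can be related to infection or its treatment (4) |
|---|---|---|---|---|
| Sepsis, phage patient: new organ failure attributed to the sepsis, not to phage | Recorded | Not recorded | Recorded | Recorded |
| Sepsis, phage patient: unexpected SAE linked by staff to neither infection nor treatment | Not recorded | Not recorded | Recorded | Not recorded |
| Musculoskeletal, phage patient: event possibly but not directly linked to treatment | Not recorded | Does not apply | Recorded | Recorded |
| Musculoskeletal control: complication of amputation | Recorded, if the rule reaches controls | Does not apply | Recorded, if the rule reaches controls | Recorded, if the rule reaches controls |
| Sepsis control: new organ failure attributed to the sepsis | Recorded, if the rule reaches controls | Not recorded, if the rule reaches controls | Recorded, if the rule reaches controls | Recorded, if the rule reaches controls |

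The first three rows show the conflict: in each, at least two applicable rules give opposite answers. The second row is the safety problem, because only statement 3 captures the event. The last two rows show that the answer for controls depends on whether rules written under the phage-group heading apply to them, which the article does not say.

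The window has the same gap. Its end is the final phage administration plus three months. A control has no such date, so the end of active AE enquiry is not defined. The date of the CBL's final treatment plan exists in both groups (sections 2.4.2 and 2.4.4).

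**Illustration only.** Suppose n intravenous patients, a true risk p of a new serious event, and a fraction c of such events that pass the filter. The chance of an empty table is (1 − p·c)^n. Assume n = 25, which is what an equal three-way split of the roughly 75 treated patients would give (75/3; section 2.3.1 states no split), and p = 0.10.

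- c = 1: 0.90^25 = 0.072, about 7%
- c = 0.5: 0.95^25 = 0.277, about 28%
- c = 0.2: 0.98^25 = 0.603, about 60%

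These values of n, p and c are assumptions. The figures show the direction of the effect and do not estimate it for this registry.

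**The case against.** The strongest reply is that the registry is descriptive and exploratory, plans no formal comparison of AE rates, asks for careful interpretation, and gives a practical reason for limiting intensive-care reporting. It is also a condensed article: AE forms and definitions may sit in the full protocol. The sepsis sentence speaks of safety parameters, so it may limit which kinds of item are recorded and not require event-by-event attribution. Could theoretically be related is also a low threshold.

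Part of this stands. Feasibility justifies limiting non-serious events on the intensive care unit. The alternative reading of the sepsis sentence is possible, and the article does not say who applies the rule. But the conflict lies between sentences that are present, not in detail left out, and feasibility is no reason to filter deaths and SAEs by attribution. A descriptive registry depends on complete ascertainment, since the counts are its product.

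Three stronger readings are tempting, and the text does not support them.

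- A reader might infer that controls record no AEs by rule. The general restriction refers to the infection or its treatment, not to phage, so complications of amputation or suppressive antibiotics would qualify. The Figure 1 legend says infection-related data are collected in either group. Only the sepsis sentence is phage-specific, and nothing says that it governs controls.
- A reader might infer that the whole safety objective is circular. Scheduled vital signs and laboratory tests in phage patients, and SOFA in sepsis, are collected without a relatedness judgement and could reveal organ toxicity. They do not replace event recording.
- A reader might infer that the data safety monitoring board sees only filtered data. The article says that it reviews possible AEs and overall outcome, but does not give the contents of its reports.

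**Conclusion.** The point holds in three parts. The recording rules contradict one another and must be reconciled. In sepsis, the phage-relatedness condition, followed as written, lets an unanticipated harm be excluded as an AE before it is recorded, against a stated principal aim. AE collection in controls is undefined, which is different from nil by rule, so the planned summaries by treatment received have no like-for-like AE comparator.

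The size cannot be derived from the article. The second part assumes that the sepsis sentence works as a condition on recording events, which is its natural reading but not the only one. The third assumes that the phage-group rules do not silently extend to controls. If they do, the window still has no end date for them.

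**What to change.** - **Deaths and SAEs.** Keep the unconditional AE/SAE sentence for these, and state that they are recorded in both groups and all three indications regardless of attribution. Do not resolve the conflict by deleting that sentence: it is the one that supports full SAE recording.
- **Relatedness.** Make it a separate field, coded after the event is on file.
- **Non-serious events in intensive care.** Replace the relatedness condition with a prespecified list drawn from data already charted, for example new organ failure by SOFA component, fever or hypotension around infusion, liver tests, creatine kinase and lactate. Apply it to controls wherever their standard of care provides the item, and report which items are unavailable.
- **Remaining non-serious events.** Choose one wording, directly related or can be related, and use it throughout.
- **Controls.** Add an AE rule to section 2.4.4. Start the control AE window at the CBL's final treatment plan, already the anchor for control follow-up, and state its length so that counts can be read against observation time.

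The cost is modest extra data entry. The feasibility concern is respected, because non-serious intensive-care events are limited to a fixed list. The change is best made early, since unrecorded events may be hard to recover later.
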